**Fig. 1 Fig1:**
[figure not shown]
CONSORT flow diagram

**Table 1 Tab1:** Characteristics of participants in the intervention, the control, and the total sample

Characteristics	Intervention (N = 27)	Control (N = 30)	Total (N = 57)
Age [M (SD)]	50.81 (11.63)	48.43 (11.99)	49.56 (11.78)
Females in sample	22 (81.5 %)	26 (86.7 %)	48 (84.2 %)
Race			
White	15 (55.6 %)	16 (53.3 %)	31 (54.4 %)
Black	9 (33.3 %)	11 (36.7 %)	20 (35.1 %)
Hispanic	3 (11.1 %)	1 (3.3 %)	4 (7 %)
Other	0	2 (6.7 %)	2 (3.5 %)
Education			
HS/Some college	5 (18.5 %)	5 (16.7 %)	10 (17.5 %)
Associates or Bachelors	7 (25.9 %)	15 (50 %)	22 (38.6 %)
Graduate Degree	15 (55.6 %)	10 (33.3 %)	25 (43.9 %)

*HS*/*Some college* High School graduate or attended some college but did not earn a degree

#### Assignment to condition

The current study is a parallel group, two arm, superiority trial with 1:1 allocation ratio. First, participants were allowed to choose whether they wanted to attend the Downtown YMCA or Southwest YMCA. Next, stratified randomization was employed such that participants were separated by race/ethnicity (i.e., minority versus non-minority) and participants were randomly assigned to the control or intervention condition within each site. A computer-generated allocation sequence was used and assignment to condition was made using sequentially numbered, opaque, sealed envelopes. Throughout the study, participants and the research assistant (i.e., an outcome assessor) will remain blind to condition. Due to the nature of the study, the exercise instructors and the experimenter (i.e., an outcome assessor and data analyst) will not be blind to condition.

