### Role and training of YMCA intervention staff

The exercise instructors who will implement the SDT and MI intervention will attend three standardized training sessions which will each last two hours long. The training and implementation of the intervention was developed based on the treatment fidelity framework, based on the Behaviour Change Consortium, to ensure the reliability within the intervention [52, 53]. Although, Miller and Rollnick [48] state that it takes approximately a decade of learning and actively using motivational interviewing to ensure proficiency, this type of training is not feasible at the YMCA. A literature review concludes that the amount of training that professionals receive in MI before conducting interventions varies greatly (i.e., less than 8 h of training to more than 24 h of training) and that the majority of these studies found positive outcomes relating to the development of MI knowledge, attitudes, basic skills, self-efficacy, interest in MI, and willingness to use MI [54]. Additionally, an intervention that examined the combined efficacy of SDT and MI on exercise and weight loss found a significant increase in exercise at the end of the 1 year intervention and 1 year post-intervention [40, 55]. This intervention used a two-day workshop in order to train their intervention staff in MI ([name], personal communication, March 5, 2014). Therefore, it is expected that the current study will produce similar results.

The training sessions will teach the instructors about SDT and MI, as well as describe why this theory and clinical technique is used within our intervention. The training sessions will be taught by a clinical psychology Ph.D. student who has used MI in clinical settings and received training in MI from a licensed clinical psychologist, and the experimenter, a social psychology Ph.D. student who read extensively about MI, watched therapists utilize MI techniques, and role-played using MI techniques with the other trainer.

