#### SDT training

To promote participants’ autonomy, instructors will give meaningful rationale for the activities and exercises used in the intervention, directions will be presented in a non-pressuring manner (e.g., “you could” versus “you should”), instructors will tailor the class to the participants’ needs and abilities so that they will experience an optimal level of challenge, and will give students choice regarding the difficulty and types of exercise used within the class [37, 58]. In order to promote participants’ sense of competence, instructors will provide participants with clear instructions during the intervention, and they will provide positive feedback when participants enact the desired behaviors [37, 58]. To satisfy participants’ relatedness needs, instructors will encourage positive relationships within the intervention setting by perspective taking, by noting verbal and non-verbal cues that indicate how participants feel during the intervention, and by working within participants’ comfort zones in order to make the intervention an interesting and rewarding experience [37, 58].

Additionally, the experimenter will meet with the exercise instructors in the intervention groups four times for half an hour during the intervention to discuss their use of SDT and MI techniques and to have them engage in a few role play exercises to strengthen certain skills. To increase the amount of practice that the instructors have using SDT and MI in the current study, the intervention exercise instructors will be encouraged to utilize these techniques within their other exercise classes and within their daily life. The experimenter will not meet with the exercise instructors in the control group during the intervention.

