### Treatment fidelity assessment

Treatment fidelity will be assessed in order to determine whether the intervention is implemented as intended and whether the intervention groups differ from the control groups in terms of their use of SDT and MI techniques. Therefore, an audio recording will be created for each exercise instructor before they are trained in SDT and MI. These recordings will be used to determine the percent of MI- and SDT-adherent components that the exercise instructors demonstrated at baseline. An audio recording will also be created for all of the intervention sessions, which will be coded every fourth week as the intervention progresses. The sessions will be coded by the experimenter (who will not be blind to condition) and a research assistant (who will be blind to condition). High inter-rater reliability will provide evidence of agreement in use of the coding technique by both coders. This information will be coded in order to allow the experimenter to assess treatment fidelity at the different sites. Deviations from SDT and MI techniques will be identified and reviewed with the exercise instructors. The Motivational Interviewing Treatment Integrity Code (MITI) version 3.1.1 [59] will be used to assess the fidelity of the motivational interviewing components of the intervention, as well as participants’ language use within the sessions. Exercise instructors’ use of MI will also be assessed by the Client Evaluation of Motivational Interviewing Scale [60]. A self-created measure based on Wilson, Griffin, Saunders, Kitzman-Ulrich, Meyers, & Mansard [61] will be used to assess the fidelity of the SDT components of the intervention.

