### Measures

Participants will complete a number of surveys during pre-intervention, session 4, session 8, and session 12. All of the data will be collected, entered into the computer, and maintained by the experimenter. A description of the primary and secondary outcome measures are listed below, as well as the measures used to assess treatment fidelity.

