### Treatment fidelity measures

#### MI techniques

Exercise instructors’ MI proficiency will be assessed at both the instructor-level and at the participant-level. The percentage of MI-adherent responses will be audio recorded using the Motivational Interviewing Treatment Integrity Code (MITI), version 3.1.1 [59]. The experimenter will code every fourth session to detect MI-adherent responses within the language that the exercise instructors use while interacting with participants. Instructors’ MI proficiency will also be assessed by the students in their classes. The Client Evaluation of Motivational Interviewing Scale [60] will be used to assess whether the participants perceive the exercise instructors to be using MI skills every fourth session. This sixteen item scale assesses two subscales: relational and technical factors associated with MI proficiency using a 4 point Likert scale which varies from 1 (never) to 4 (a great deal). An example of the relational factors includes the item, “The exercise instructor changed the topic when I became upset about changing my behavior.” A technical item is, “The exercise instructor helped you talk about changing your behavior.”

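### One unblinded person who trains and coaches the intervention side also handles and analyses all the data, although a blinded assistant is in place: an avoidable risk of bias of unknown size

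*Protocol article*

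**What the plan says.** All references are to the protocol article.

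- **Assignment to condition.** Participants and one assessor are masked: "participants and the research assistant (i.e., an outcome assessor) will remain blind to condition". The experimenter is not: "the experimenter (i.e., an outcome assessor and data analyst) will not be blind to condition". One reason covers both unblinded roles: "Due to the nature of the study, the exercise instructors and the experimenter".
- **Measures.** "All of the data will be collected, entered into the computer, and maintained by the experimenter". The assistant is given no part in this.
- **Role and training of YMCA intervention staff.** The SDT/MI training has two teachers, a clinical psychology student "and the experimenter, a social psychology Ph.D. student who read extensively about MI".
- **SDT training.** The experimenter has four half-hour meetings with the intervention instructors while the classes run. For the other arm, "The experimenter will not meet with the exercise instructors in the control group during the intervention".
- **Treatment fidelity assessment.** "The sessions will be coded by the experimenter (who will not be blind to condition) and a research assistant (who will be blind to condition". Agreement between the two is to be reported as evidence of reliability.
- **MI techniques.** "The experimenter will code every fourth session to detect MI-adherent responses". No second coder is mentioned here.
- **Planned statistical analyses.** A 2 × 2 ANCOVA with pretest covariates is set for physical activity by IPAQ, analysis of variance for the secondary outcomes, and a bootstrap for mediation.
- **Discussion.** The limitations are self-report and the mismatch in race/ethnicity between instructors and participants. The unblinded data handling and analysis are not among them.

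**The concern.** The person with the closest involvement in making the intervention work also controls the data from receipt of the forms to the result, and knows each participant's arm throughout. Between those two points lie judgements that are easy to make differently by arm without intending to: reading an unclear entry, handling an implausible IPAQ duration, deciding whether a record is usable. With 57 participants, a few such decisions can matter.

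Fidelity scoring is the more direct exposure. There the experimenter rates instructors whom the experimenter helped to train and then coached, and compares them with instructors who received neither. That comparison is meant to show that the arms differed in SDT and MI content.

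What makes this worth raising is that most of it can be avoided with the people already on the study.

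**Working it through.** The plan gives no figure on this point, so the check is a comparison of sections plus one count. The sample size of 48 does not depend on who is blind.

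**1. Who does what, and must arm be known to do it?**

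| Task | Assigned to | Does the task need knowledge of arm? |
|---|---|---|
| Teaching SDT/MI to instructors | Experimenter and one other trainer | Yes |
| Coaching during the trial | Experimenter, intervention side only | Yes |
| Collecting surveys in class | Experimenter | Hard to avoid |
| Entering forms | Experimenter | No |
| Scoring, cleaning, exclusions | Not assigned separately; falls to the experimenter as holder of the data and analyst | No |
| Running the models | Experimenter | Only once the data are fixed |
| Coding recordings | Experimenter and blinded assistant | No, though content may reveal it |

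The stated reason covers the first three rows. It does not reach entry, scoring, cleaning or exclusions.

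**2. Is there someone else?** Yes. The assistant is described as a blinded outcome assessor and as second fidelity coder.

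**3. Can the assistant take over everything?** No. Table 2 places surveys in sessions 1, 4, 8 and 12, and most intervention sessions carry worksheets or group discussion that the control classes do not have. Someone collecting forms in the room would probably learn the arm. The attendance record described under Physical activity is kept by control or intervention class, so extracting it also reveals the arm. Either task would put at risk the blinding on which the assistant's fidelity coding depends. Entering completed forms by study ID does not carry that problem to the same degree.

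**4. Would A/B labels mask the analyst?** No. Table 1 gives:
- intervention: 15 White and 9 + 3 + 0 = 12 minority, total 15 + 12 = 27;
- control: 16 White and 11 + 1 + 2 = 14 minority, total 16 + 14 = 30;
- overall: 27 + 30 = 57.

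Anyone who tabulates the label sees 27 and 30 and knows which arm is which. The arm variable has to be absent from the file, not renamed.

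**5. Do the two fidelity sections conflict?** One names two coders. The other names the experimenter and is silent on a second. It does not say that the experimenter codes alone. This is a wording gap to close, and not proof that the second coder was dropped.

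**The case against.** The case for leaving the plan as it is has real strength.

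- **The primary outcome is not rated by anyone.** Participants complete the IPAQ and are stated to be blind, and attendance comes from YMCA records. This stands, and it limits the exposure to what happens after the form is filled in.
- **The models are fixed.** A reader might infer that the experimenter is free to pick the model with arms in view. The planned analyses name the models, so that is not supported. Scoring, cleaning and exclusion rules may be set in a fuller protocol or analysis plan that is not shown, and their absence from the article is not a fault. Even written rules have to be applied to individual records, and that step can be masked.
- **The role is disclosed.** True. This is a design weakness openly stated, and not an error of fact.
- **Fidelity already has a blinded coder.** True. A reader might infer that the experimenter codes everything, or that no inter-rater agreement can be computed. The section on treatment fidelity contradicts both.

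A reader might also want to express the risk as an inflated type I error, by supposing that the best of several outcome codings is kept. The document gives neither the number of codings nor their correlation. Picking the smallest two-sided p-value also needs no knowledge of arm, so such a figure would measure unfixed coding, and masking would not remove it.

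**Conclusion.** The concern holds as an avoidable **risk** of bias. The documents do not show that bias occurred or will occur, and its size cannot be computed from them. The risk lies in data entry, IPAQ scoring, exclusions and fidelity scoring. It is limited on the self-completed IPAQ and plainest in fidelity scoring, where a second, blinded coder already gives partial protection.

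The conclusion rests on two readings of the text: that giving all data handling to the experimenter means what it says, and that the assistant's blinding can be kept if that person stays out of the classes and the class registers. The change is inexpensive and worth making; the point does not undermine the trial's design.

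**What to change.** 1. **Measures.** Amend so that the blinded research assistant enters the completed survey forms by a study ID that does not encode arm, class or instructor.
2. **Before analysis.** Complete and lock IPAQ scoring, cleaning and exclusions on a file without the arm variable, and without class or instructor, which would stand in for it. Then merge arm and run the models already planned. Do not rely on A/B labels.
3. **Keep the assistant blind.** Leave in-class survey collection and extraction of class attendance with other staff roles.
4. **MI techniques.** Name both coders, in line with the section on treatment fidelity. Report the blinded coder's scores as the fidelity result, use the experimenter's scores for agreement, and note that the recordings may partly reveal the arm.

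Cost: some hours of data entry move to the existing assistant, and one merge step is added before analysis. No new staff are needed, and nothing in the intervention or the models changes. The masking remains partial, because the experimenter will still know the arms from the coaching and the classes.

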### SDT and MI Intervention

All participants will participate in 12 weekly sessions for one hour with a YMCA instructor who has been trained to teach exercise classes. A brief intervention will be utilized because past research suggests that brief interventions based on both SDT and MI can increase participants’ physical activity and physical activity adherence over time [38, 41]. Participants in the intervention groups will engage in group discussions led by an SDT and MI-trained exercise instructor and will engage in exercise. The control groups will be taught by an exercise instructor who will not be trained in SDT and MI. The participants in the control groups will engage in exercise classes that are not based on any clinical or theoretical basis. This is an appropriate comparator since the control sessions closely resemble group exercise classes that are traditionally taught at gyms. Figure 2 shows a timeline for the intervention.

**Fig. 2 Fig2:**
[figure not shown]
Timeline for the SDT and MI Intervention

#### Intervention sessions

The MI techniques that will be used in the intervention sessions are primarily based on information from the books, Motivational Interviewing, Third Edition: Helping People Change and Motivational Interviewing in Groups [48, 49]. The Diabetes Prevention Program, a motivational program to increase physical activity and healthy eating, informs some of the curriculum that will be used during the intervention [50]. Additionally, articles by Williams et al. [51] and Edmunds, Ntoumanis, & Duda [37] inform the SDT techniques that will be used within the intervention. The content of the intervention sessions are described in Table 2. The exercise instructors have some flexibility during their classes in regards to what they decide to discuss within the class. There are two sessions (session 10 and 11), which are not designed to include specific material. Therefore, the instructors can decide to change the treatment protocol by discussing any issues that they believe would help the class during two sessions. They can decide to implement these sessions any time after the first session. The instructors’ standardized treatment manual will facilitate SDT- and MI-adherent conversations, but the program will be tailored to the needs of the group.

**Table 2 Tab2:** Activities during the twelve intervention sessions

	Sessions											
	1	2	3	4	5	6	7	8	9	10	11	12
Aerobic and muscle-strengthening exercises	✓	✓	✓	✓	✓	✓	✓	✓	✓	✓	✓	✓
Pre and post-test survey	✓											✓
Worksheet: Music for class and how to use Facebook page	✓											
Worksheet and Class Discussion: Values, goals, and how PA fits in their lives		✓										
Worksheet: Types of PA they enjoy, Class Discussion: What they know about PA, more information about PA			✓									
Short IPAQ and CEMI				✓				✓				
Class Discussion: Feedback about the PA they do versus the CDC Guidelines				✓								
Worksheet and Class Discussion: If participant wants to change the amount or type of PA they do, confidence strengthening worksheet; if participant doesn’t want to change their PA, barriers to change worksheet.					✓							
Worksheet and Class Discussion: If participant want to change PA, signed contract describing their plan to change; if they don’t want to change PA, barriers to change worksheet.						✓						
Instructor has individual discussions with participants who do not have a plan to change their PA.							✓					
Worksheet and Class Discussion: Assess current level of progress with PA change. If unsuccessful, develop new plan.								✓				
Class Discussion: PA with family, friends and pets									✓			
Class Discussion: Instructor decides on topic and leads an SDT and MI-consistent discussion										✓	✓	
CEMI and Survey about participants’ perception of the study												✓

*Pre and post*-*test survey* The consent form, Demographics (age, sex, race, education, and income information), The Support for Exercise Habit Scale, Basic Psychological Needs in Exercise Scale, Behavioural Regulation in Exercise Questionnaire, The Integrated Regulation Items, and The Psychological General Well-Being Index, *PA* Physical Activity, *Short IPAQ and CEMI* Short version of the International Physical Activity Questionnaire and the Client Evaluation of Motivational Interviewing Scale

### Role and training of YMCA intervention staff

The exercise instructors who will implement the SDT and MI intervention will attend three standardized training sessions which will each last two hours long. The training and implementation of the intervention was developed based on the treatment fidelity framework, based on the Behaviour Change Consortium, to ensure the reliability within the intervention [52, 53]. Although, Miller and Rollnick [48] state that it takes approximately a decade of learning and actively using motivational interviewing to ensure proficiency, this type of training is not feasible at the YMCA. A literature review concludes that the amount of training that professionals receive in MI before conducting interventions varies greatly (i.e., less than 8 h of training to more than 24 h of training) and that the majority of these studies found positive outcomes relating to the development of MI knowledge, attitudes, basic skills, self-efficacy, interest in MI, and willingness to use MI [54]. Additionally, an intervention that examined the combined efficacy of SDT and MI on exercise and weight loss found a significant increase in exercise at the end of the 1 year intervention and 1 year post-intervention [40, 55]. This intervention used a two-day workshop in order to train their intervention staff in MI ([name], personal communication, March 5, 2014). Therefore, it is expected that the current study will produce similar results.

The training sessions will teach the instructors about SDT and MI, as well as describe why this theory and clinical technique is used within our intervention. The training sessions will be taught by a clinical psychology Ph.D. student who has used MI in clinical settings and received training in MI from a licensed clinical psychologist, and the experimenter, a social psychology Ph.D. student who read extensively about MI, watched therapists utilize MI techniques, and role-played using MI techniques with the other trainer.

#### MI training

The instructors will learn about the spirit of MI (i.e., encouraging a partnership, providing acceptance, compassion and evoke individuals’ motivation to change), the four general principles of MI (i.e., express empathy, develop discrepancy, avoid argumentation, roll with resistance, and support self-efficacy), and how to use MI microskills (i.e., asking open-ended questions, using affirmations, using reflections, and using summaries) [56]. Instructors will also use exercises from the Motivational Interviewing Training for New Trainers, role-play situations (initially playing the role of the student and then take the role of the instructor), review the treatment manual, and watch taped sessions that depict the use of MI (i.e., MI spirit and microskills) [48, 57].

